## Abstract

**Background::**

Schizophrenia primarily depends on pharmacotherapy, which has demonstrated limited efficacy in enhancing cognitive impairments. High-definition transcranial direct current stimulation (HD-tDCS) and computerized cognitive remediation therapy (CCRT) hold potential for improving cognitive impairments. This study aims to investigate the effects of combining HD-tDCS with CCRT on cognition and to explore the mechanisms of this approach in schizophrenia.

**Study Design::**

This is the protocol of a randomized controlled trial.

**Methods::**

Schizophrenia patients will be randomly assigned to one of 4 groups: HD-tDCS + CCRT group (Group 1), HD-tDCS group (Group 2), CCRT group (Group 3), and a control group (Group 4). The central electrode will be personalized using magnetic resonance imaging (MRI)-guided localization in the medial prefrontal cortex (mPFC). CCRT includes 6 therapeutic modules and 10 distinct tasks. Both HD-tDCS and CCRT will be administered once daily, 5 days per week, for 4 consecutive weeks, culminating in a total of 20 sessions. Assessments will occur at baseline (T0), after 10 sessions (T1), after 20 sessions (T2), and after 6 months of follow-up (T3). The primary outcome measure is the change in cognition. We will employ multimodal MRI, serum concentrations of brain-derived neurotrophic factor (BDNF) and glial cell line-derived neurotrophic factor (GDNF) to explore the underlying mechanisms.

**Expected Results::**

An involvement of mPFC and synaptic plasticity in response to HD-tDCS and CCRT is hypothesized.

**Conclusion::**

The study will provide empirical evidence for the effectiveness of combined therapy at an individual level, explore its mechanisms, and may ultimately result in personalized medicine.

**Clinical Trial Registration::**

ChiCTR2500102731, https://www.chictr.org.cn/hvshowprojectEN.html?id=276964&v=1.0.

## Main Points

1. High-definition transcranial direct current stimulation (HD-tDCS) targeting 
the medial prefrontal cortex (mPFC) holds promise for enhancing cognitive 
functions in patients with schizophrenia.

2. Combining HD-tDCS with computerized cognitive remediation therapy (CCRT) 
might lead to more significant cognitive enhancements than using each treatment 
separately.

3. The biological mechanisms underlying the synergistic effects of HD-tDCS and 
CCRT on cognitive functions will be explored.

## 1. Introduction

Schizophrenia is a severe, chronic, and disabling mental disorder with an 
etiology that remains largely elusive. Clinically, it is characterized by 
cognitive impairments, negative symptoms, and positive symptoms [1]. Cognitive 
impairment is recognized as a core feature of schizophrenia, affecting various 
domains including working memory, language, verbal fluency, attention, reading 
ability, processing speed, and non-verbal reasoning [2, 3]. These impairments 
significantly impact patients’ social functioning and daily living skills, 
further perpetuating the stigma associated with mental illness and creating a 
detrimental cycle [4]. Schizophrenia poses multifaceted societal burdens, 
primarily manifesting as economic challenges, caregiving demands, emotional 
stress, and enduring pressures [5, 6]. While pharmacological treatments for 
schizophrenia, such as antipsychotic medications, are well-established and 
primarily effective in alleviating positive symptoms, their efficacy in improving 
cognitive impairments remains limited [7, 8]. Certain antipsychotic medications, 
notably first-generation agents and clozapine, have been associated with 
detrimental cognitive effects, a consideration that is critical in clinical 
decision-making [9]. Furthermore, pharmacological treatments are often 
accompanied by substantial economic burdens for families, low adherence rates, 
and potential adverse effects, including extrapyramidal symptoms as well as 
endocrine and metabolic disturbances [10]. Consequently, it is imperative to 
explore non-pharmacological interventions, such as neuro-modulation therapy and 
cognitive remediation, to ameliorate cognitive impairments in individuals with 
schizophrenia.

Transcranial direct current stimulation (tDCS) represents a non-invasive 
neuromodulatory approach employed in the treatment of schizophrenia, 
characterized by its low cost and reliable safety profile [11, 12]. Its mechanism 
may involve modulating the resting state of neuron membranes, thus affecting 
neuronal excitability [13]. High-definition transcranial direct current 
stimulation (HD-tDCS) is an advanced tDCS technology, offering the distinct 
advantage of delivering electrical currents with greater precision to targeted 
brain regions, thereby enhancing both accuracy and durability of effects [14, 15]. Recent studies have demonstrated that tDCS can improve attention, working 
memory, and social cognitive abilities in individuals with schizophrenia [16]. 
HD-tDCS has been shown to assist healthy individuals in more accurately assessing 
their memory status and enhancing working memory [17, 18]. Furthermore, HD-tDCS 
has demonstrated potential in ameliorating cognitive deficits in individuals with 
chronic schizophrenia [19]. In contemporary research involving patients with 
schizophrenia, the anodal stimulation site for most tDCS/HD-tDCS interventions is 
typically the left dorsolateral prefrontal cortex. However, studies have observed 
that alterations in neural activity within the medial prefrontal cortex (mPFC) 
are associated with decreased accuracy in reality monitoring tasks among 
schizophrenia patients [20]. In this population, inadequate deactivation of the 
mPFC during working memory tasks may significantly contribute to memory 
impairments [21]. Consequently, HD-tDCS targeting mPFC holds promise for 
enhancing cognitive performance in patients with schizophrenia. However, it is 
important to acknowledge that the effects of non-invasive brain stimulation can 
be inconsistent, and the cognitive improvements it offers may be challenging to 
sustain over the long term [22, 23]. Therefore, investigating the integration of 
non-invasive brain stimulation with other cognitive interventions that have more 
enduring effects, such as cognitive remediation therapy (CRT), to achieve 
synergistic and sustained enhancements, represents a promising avenue for future 
research.

CRT is an evidence-based intervention that has been demonstrated to enhance 
cognition in schizophrenia [24]. This has facilitated the development of a 
computerized variant, known as computerized CRT, which seeks to augment patients’ 
cognitive abilities through digital training programs [25, 26]. Computerized 
cognitive remediation therapy (CCRT) utilizes computer technology to deliver both 
standardized and individualized training tasks, thereby allowing for more precise 
and tailored therapeutic interventions targeting the cognitive functions. Several 
pieces of evidence suggest that CCRT can enhance both cognitive abilities and 
social functioning in individuals with schizophrenia [27, 28]. Moreover, the 
cognitive and social improvements facilitated by CCRT have been observed to 
persist for up to 6 months post-therapy [29]. Despite these promising outcomes, 
the efficacy of CCRT varies significantly among patients [30]. Some research 
indicates that CCRT does not produce substantial cognitive improvements in 
certain cases of schizophrenia [31]. Consequently, further clinical and 
mechanistic investigations are warranted to elucidate the effectiveness of CCRT 
in schizophrenia.

Combining HD-tDCS with CCRT might lead to more significant cognitive 
enhancements than using each treatment separately. A preliminary study indicated 
that the combination of tDCS and CRT led to improvements in cognitive domains 
such as visual memory, processing speed, and working memory, with these 
enhancements persisting one month post-therapy [32]. Another study involving 49 
participants demonstrated that CRT paired with active tDCS significantly improved 
working memory in patients with schizophrenia, compared with CRT with sham tDCS, 
with these improvements sustained over an extended period of 56 days [33]. 
However, concerning clinical symptomatology, one study reported that CRT combined 
with active tDCS did not yield significant therapeutic effects on clinical 
symptoms in schizophrenia patients when compared to CRT with sham tDCS [34]. It 
is worth noting that the aforementioned study had a limited sample size, 
potentially impacting its statistical power. Consequently, the researchers 
recommended conducting larger-scale controlled trials to more comprehensively 
evaluate the potential benefits of combining CRT with CCRT. Research on tDCS in 
conjunction with CRT has demonstrated a positive impact on cognitive enhancement 
in individuals with schizophrenia. Currently, there is a lack of direct research 
examining the combined use of HD-tDCS and CCRT in schizophrenia patients.

Previous research has demonstrated that both HD-tDCS and CCRT independently 
enhance cognitive function in individuals with schizophrenia. However, studies 
investigating their combined application remain scarce. Schizophrenia is widely 
recognized as a disorder characterized by dysconnectivity within brain networks, 
particularly involving functional abnormalities in key brain regions such as the 
limbic system, temporal lobe, and parietal lobe, which correlate with the 
severity of cognitive deficits [35, 36]. Functional magnetic resonance imaging 
(fMRI) is utilized to indirectly assess neural activity in patients with 
schizophrenia by measuring blood oxygen level-dependent signals, thereby 
facilitating a comprehensive examination of treatment-induced changes in brain 
activity [37]. Importantly, prefrontal-temporal tDCS has been shown to modulate 
dysfunctional network connectivity in patients with schizophrenia, underscoring 
the potential of neuromodulation to target circuit-level deficits [38]. Moreover, 
tDCS not only modulates the activity and connectivity of cortical and subcortical 
brain networks but also influences blood concentrations of biomarkers such as 
brain-derived neurotrophic factor (BDNF) and glial cell line-derived neurotrophic 
factor (GDNF). These systemic alterations collectively form the biological basis 
for its therapeutic effects [39]. BDNF and GDNF function as critical biomarkers 
for synaptic plasticity, a process involved in the pathogenesis and treatment of 
schizophrenia [40]. The hypothesized mechanisms underlying HD-tDCS, particularly 
its enhancement of long-term memory, include the upregulation of BDNF expression, 
activation of its signaling pathway, and improved synaptic plasticity [41]. 
Similarly, studies on CCRT have demonstrated its effectiveness in enhancing 
cognitive function in schizophrenia, accompanied by observed increases in serum 
GDNF levels [42]. Moreover, the literature also proposes that serum BDNF and GDNF 
levels might represent the central nervous system’s BDNF and GDNF expression 
profile [43, 44]. BDNF is essential for neuronal synthesis, 
differentiation, maintenance, and survival. Studies have demonstrated a 
correlation between decreased peripheral blood BDNF levels and cognitive 
impairments, such as attention deficits, in individuals with schizophrenia 
[45, 46, 47]. GDNF levels have been associated with working memory performance and 
attention deficits [48]. As far as we know, no research has investigated the 
combined effects of magnetic resonance imaging (MRI)-guided HD-tDCS targeting 
mPFC and CCRT on cognitive deficits, nor the biological mechanisms underlying 
their combined use in treating schizophrenia.

The current study aims to achieve three primary objectives. The primary aim of 
this study is to evaluate the synergistic effects of HD-tDCS and CCRT on 
cognitive abilities and clinical symptoms through a randomized controlled trial. 
We hypothesize that the combined HD-tDCS and CCRT intervention will result in 
greater cognitive improvement in individuals with schizophrenia compared to 
either intervention alone. The secondary aim is to evaluate the long-term impacts 
of HD-tDCS and CCRT after a six-month period. The third aim is to investigate the 
biological mechanisms of MRI-guided HD-tDCS and CCRT in schizophrenia, utilizing 
MRI, and measuring serum BDNF and GDNF levels. This study not only promises to 
contribute to the development of innovative therapeutic strategies for 
schizophrenia but also seeks to enhance our understanding of its pathophysiology.

## 2. Methods

### 2.1 Study Design 

This study is a prospective, double-blind, randomized controlled trial protocol 
to assess the efficacy of HD-tDCS combined with CCRT in enhancing cognitive 
function among patients with schizophrenia. Eligible participants will be 
recruited and randomly allocated into four groups using a random number table: 
the HD-tDCS + CCRT group (Group 1), the HD-tDCS group (Group 2), the CCRT group 
(Group 3), and the control group (Group 4). Assessments will be carried out at 
baseline (T0), after 10 sessions (T1), after 20 sessions (T2), and after six 
months of follow-up (T3). Research framework is illustrated in Fig. 1. 
Participants in the control group (Group 4) will continue to receive their stable 
regimen of antipsychotic medication and standard clinical care, without 
undergoing any HD-tDCS or CCRT sessions.

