### 2.2 Recruitment and Eligibility Criteria

This trial will be conducted at the Second Affiliated Hospital of Xinxiang 
Medical University. Eligible individuals will adhere to the following inclusion 
criteria: (1) According to the Diagnostic and Statistical Manual of Mental 
Disorders, Fifth Edition (DSM-5), the individual meets the clinical criteria for 
schizophrenia. (2) Patients who maintain stability with oral antipsychotic 
medication are defined by the following criteria: a score of ≤5 on the 
items of exaggeration, delusion, suspiciousness/victimization, and hallucinatory 
behavior in the Positive and Negative Symptom Scale (PANSS), and a score of 
≤4 on the PANSS conceptual disorganization. (3) Currently, treatment 
involves atypical antipsychotic drugs, with their equivalent doses calculated 
using the defined daily dose method. (4) Individuals aged 18 to 50 years. (5) 
Educated at the primary school level or higher, and able to comprehend and 
collaborate to finish the trial. Exclusion criteria: (1) Patients are undergoing 
the acute phase of the disease and cannot cooperate in completing the examination 
and operational tasks under guidance. (2) Organic brain lesions, intellectual 
disabilities, or other severe physical illnesses. (3) Currently undergoing other 
neurostimulation therapies or evidence-based psychotherapy. (4) There are 
indications related to contraindications for HD-tDCS. (5) There are visual 
impairments or significant eye diseases, such as color blindness, color weakness, 
cataracts, etc. (6) Substance abuse and addiction. (7) Women who are pregnant or 
breastfeeding.

Clinical professionals who are qualified will conduct the evaluation of 
potential participants using the inclusion and exclusion criteria. Eligible 
individuals will receive comprehensive verbal and written details about the 
study’s benefits, risks, and precautions from psychiatrists. Upon consenting to 
participate, both the participants and their legal guardians are required to 
provide their signatures on an informed consent form. The trial 
will be carried out according to the 2013 Standard Protocol Items: Recommendations for Interventional Trials (SPIRIT) statement guideline for trial 
protocols [49]. See Table 1 and **Supplementary Material**.

**Table 1. S3.T1:** **World Health Organization trial registration data set related 
to this study**.

Data category	Information
Primary Registry and Trial Identifying Number	ChiCTR2500102731

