### 2.3 Randomization 

Randomization will be performed by a statistician who does not take part in the 
study. All eligible participants will be allocated into four groups using a 
computer-generated random number table. Each assigned a specific group number: 
HD-tDCS + CCRT (Group 1), HD-tDCS (Group 2), CCRT (Group 3), and control (Group 
4). For the randomization process, personnel employed Microsoft Excel 2019 
software (Microsoft Corp., Redmond, WA, USA) to enter 48 participants into a spreadsheet, assigning each a unique 
identifier ranging from “1–48”. They then used the “=RAND()” function to 
generate a random number for each assigned number. Subsequently, these random 
values were fixed using the “Paste Special” dialog box. Following this, the fixed 
random values were sorted in descending order. The sorted numbers were then 
divided into four groups, each comprising 12 numbers, resulting in a total of 48 
numbers. This procedure effectively randomized the 48 patients into four groups, 
with each group consisting of 12 individuals. Once the randomization scheme was 
established, it was secured in opaque envelopes, which were opened sequentially 
according to the order of participant enrollment. The allocation scheme within 
each envelope determined the group assignment for each patient. This method 
ensured that study personnel could not compromise the randomization process by 
having prior knowledge of the randomization scheme. The progression of 
participants through the screening, randomization, therapy, and follow-up stages 
is illustrated in Fig. 2.

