### 2.5 MRI Scanning

All participants will receive MRI scans at T0, T1, T2, and T3. MRI scans will be 
conducted in the Department of Radiology at the Second Affiliated Hospital of 
Xinxiang Medical University. The scanning procedures will be performed by 
radiologists who are proficient in MRI operation. A 3.0T MRI scanner (MAGNETOM 
PRISMA, Siemens Healthineers, Erlangen, Germany) will be used for the scans. 
Structural T1-weighted MRI images will be acquired using a 3D MPRAGE sequence 
with the following parameters: Field of View (FOV) = 224 × 224, flip 
angle = 8 degree, Repetition Time (TR) / Echo Time (TE) / Inversion Time (TI) = 
2400/2.14/1000 ms, voxel size = 0.7 mm isotropic, Bandwidth (BW) = 210 Hz/pixel, 
integrated Parallel Acquisition Techniques (iPAT) = 2. T2-weighted images will be 
obtained using a 3D T2-SPACE sequence, with the following parameters: TR/TE = 
3200/565 ms, flip angle variable, FOV = 224 × 224, voxel size = 0.7 mm 
isotropic, BW = 755 Hz/pixel, iPAT = 2. Resting-state MRI data will be acquired 
using a gradient echo planar imaging sequence with the following parameters: TR = 
2000 ms, TE = 30 ms, FOV= 220 mm × 220 mm, slice thickness = 4 mm, 
inter-slice gap = 0.6 mm, number of slices = 33, in-plane resolution = 64 
× 64, flip angle = 90°.

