### 2.9 Outcome

The primary outcome measure used in this research is the MATRICS Consensus 
Cognitive Battery (MCCB), which is a crucial tool for assessing cognitive 
deficits in schizophrenia. It evaluates seven distinct cognitive domains: working 
memory, abstract thinking, attention/vigilance, processing speed, visual 
learning, verbal/visual learning, reasoning and problem-solving. The battery 
comprises the following subtests: (1) Trail Making Test A (TMT-A), (2) Symbol 
Coding, (3) Hopkins Verbal Learning Test-Revised (HVLT-R), (4) Digit Span Test 
(DST), (5) Stroop Color-Word Test, (6) Spatial Span Test (derived from the 
Wechsler Memory Scale III, WMS-III), (7) Verbal Fluency Test (VFT), (8) Mazes, 
(9) Brief Visuospatial Memory Test-Revised (BVMT-R), and (10) Continuous 
Performance Test-Identical Pairs (CPT-IP).

Secondary outcome measures include the Brief Psychiatric Rating Scale (BPRS), 
the PANSS, the Clinical Global Impression 
(CGI) scale, the Social Disability Screening Schedule (SDSS), the Schizophrenia 
Quality of Life Scale (SQLS), and fMRI. Specifically, the general information 
questionnaire is utilized to collect basic information about the patients. BPRS 
primarily assesses the severity of psychotic symptoms, with total scores ranging 
from 18 to 126, where higher scores reflect more severe symptoms. PANSS is used 
to evaluate the presence and severity of various symptoms. CGI scale is applied 
to assess the patient’s overall condition and therapeutic efficacy. SDSS measures 
the extent of social functional deficits. SQLS is designed to evaluate the 
quality of life in schizophrenia. For detailed information, please see Table 2.

**Table 2. S3.T2:** **Schedule of enrollment, interventions, assessments, and visits 
of patients**.

	Recruitment	Baseline	Assessments		
			Weekend 2	Weekend 4	6-month follow-up
Time point		T0	T1	T2	T3
Prescreening for eligibility, consenting and clinical interview					
Recruitment					
Eligibility screening	√				
Informed consent	√				
Allocation	√				
Primary outcome assessment					
MCCB		√	√	√	√
Second outcome assessment					
BPRS		√	√	√	√
PANSS		√	√	√	√
CGI		√	√	√	√
SDSS		√	√	√	√
SQLS		√	√	√	√
GIQ		√			
MRI		√	√	√	√
Blood sample collection (BDNF and GDNF levels)		√		√	√
Safety					
ARS			√	√	

A checkmark (√) indicates the time point at which each assessment is 
carried out. MRI, magnetic resonance imaging.

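### Table 2 schedules allocation before the T0 assessments in a trial without sham, so the baseline MCCB is a post-randomisation measurement left open to knowledge of the arm

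*Protocol article*

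**What the plan says.** All places are in the protocol article.

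- **Order of steps, text.** Section 2.1 has eligible patients "recruited and randomly allocated into four groups using a random number table" and then lists assessments from T0 to T3. Section 2.3 begins "All eligible participants will be allocated into four groups using a" computer-generated list, and has opaque envelopes opened one after another "according to the order of participant enrollment". Neither section says whether T0 is complete when the envelope is opened.
- **Order of steps, schedule.** In Table 2 (section 2.9), "Eligibility screening", consent and allocation are all ticked in the Recruitment column. MCCB, PANSS, MRI and blood have their first tick in the next column, Baseline (T0).
- **Primary outcome.** The abstract states: "The primary outcome measure is the change in cognition". Section 2.9 names the MCCB as the measure.
- **Sham and blinding.** Group 4 has no sessions of either kind (2.1), and the limitations paragraph of the Discussion concedes that sham controls are lacking. Section 2.4 nevertheless declares patients and raters blinded and reserves knowledge of group membership for the principal investigator. The same section has that investigator give each of four separate therapy teams its own protocol, to be applied to its assigned patients.
- **Analysis set.** Section 2.11 commits all analyses to intention-to-treat by randomised group, using linear mixed-effects models.

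**The concern.** A baseline is protected by randomisation only if it is measured before anyone can act on the assignment. Here the only place that fixes the order puts the assignment first. The MCCB depends on effort. A patient who has learned, or guessed from the arrangements being made, that no sessions will follow may perform differently at T0 from one who expects two therapies. Such a difference would sit in the reference value from which every change is measured.

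The second risk does not depend on unblinding. Anyone who leaves between allocation and T0 has been randomised but has no cognitive score at any visit.

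**Working it through.** No figure in the plan bears directly on this point, so the check sets the passages side by side. Short algebra then shows what a disturbed T0 would do.

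**1. Does any passage put T0 before allocation?**

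| Place | What it fixes |
|---|---|
| 2.1 | Eligible first, then allocated; T0 not placed relative to allocation |
| 2.3 | Sequence of envelopes follows enrolment; no link to T0 |
| Table 2 | Allocation under Recruitment; T0 assessments in the following column |
| 2.4 | Who holds the assignments; not when they reach the therapy teams |

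Only Table 2 fixes an order, and it places allocation before T0. Nothing in the text contradicts it.

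**2. Effect on the contrast.** Let d0 be the difference between two arms in T0 MCCB caused by knowing the arm, d2 the same at T2 (both in SD units), and ρ the T0–T2 correlation. Assume equal SDs at the two visits. With no therapy effect:

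- bias of the change-score contrast = d2 − d0
- bias with T0 as covariate = d2 − ρ·d0

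The documents give none of these quantities. For illustration, assume d0 = 0.1 to 0.3 SD and ρ = 0.5 to 0.8.

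- *Effect present at T0 and gone by T2 (d2 = 0).* Change score: 0.1 to 0.3 SD in absolute value. Adjusted for T0: from 0.5 × 0.1 = 0.05 to 0.8 × 0.3 = 0.24 SD. Adjustment shrinks the bias but does not remove it.
- *Effect equally large at T2 (d2 = d0).* Change score: 0. Adjusted: (1 − ρ)·d0, from 0.2 × 0.1 = 0.02 to 0.5 × 0.3 = 0.15 SD.

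The sign is also open. Disappointment lowering Group 4 at T0, or expectation raising Group 1 at T0, makes d0 positive for Group 1 minus Group 4. If it has gone by T2, it works *against* the combination. Other reactions could work the other way.

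**3. Loss between allocation and T0.** There are 48 patients in four groups, so 48/4 = 12 per arm. A patient with no MCCB at any visit supplies no outcome to the mixed model. Each one removes 1/12 = 8.3% of an arm from an analysis described as intention-to-treat.

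**4. PANSS and eligibility.** Inclusion criterion 2 in section 2.2 sets ceilings on the PANSS "items of exaggeration, delusion, suspiciousness/victimization, and hallucinatory" behaviour items and on conceptual disorganization. Table 2 has no PANSS tick before T0, so the article does not show which rating decides this criterion.

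**The case against.** The strongest reply is that the case rests on one tick in a table. Sections 2.1 and 2.3 do not place T0 after allocation, and Figures 1 to 3 and the supplementary material, which could not be checked here, may show another order. This stands as a limit on certainty. If they differ from Table 2, the places must be reconciled, and the remedy is the same.

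Next, a reader might infer that patients *do* know their arm at T0. The documents do not say so. Section 2.4 restricts disclosure, section 2.10 uses outside blinded physicians for the ratings, and lack of sham reveals the arm mainly once sessions start or fail to start. What remains is a risk: assignments must reach the therapy teams, no passage delays that until after T0, and measuring T0 first would protect it whether or not blinding succeeds.

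A reader might also infer that eligibility is settled only after randomisation, because "Organic brain lesions" are an exclusion and section 2.5 says "All participants will receive MRI scans at T0, T1, T2, and T3". That is not supported. Screening has its own tick at Recruitment, and only eligible patients are randomised. MRI is described for head modelling, targeting and outcome, never as an eligibility test. The T0 PANSS can be read as an outcome baseline, and other criteria also lack a row of their own. Only the question of which PANSS rating serves criterion 2 survives.

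Finally, section 2.11 already allows for 20% dropout. That protects numbers; it does not make the patients lost before T0 comparable across arms or give them an outcome value. It is true, however, that no passage describes such withdrawals, so their number is unknown.

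**Conclusion.** The scheduling defect holds and should be corrected. As Table 2 stands, the T0 MCCB is measured after randomisation in a trial without sham, and the text contains no safeguard that puts T0 first.

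No size can be given for the bias. The SD figures above rest on an assumed shift and correlation, and the change-score bias vanishes if the shift persists unchanged to T2. They show only that baseline adjustment is not a full remedy. They do not support a claim of inflated false-positive rates in favour of the combination, and a two-arm contrast is in any case not the planned HD-tDCS × CCRT interaction model. The one firm figure is that each patient lost before T0 is 8% of an arm. Confidence is medium, because the order rests on Table 2 alone.

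**What to change.** - In Table 2, move the allocation tick to after the Baseline column.
- In 2.1 and 2.3, state that the next envelope is opened only once all T0 assessments (MCCB, PANSS, other scales, MRI, blood) are complete, and that a patient who withdraws before then is not randomised.
- State which PANSS rating serves inclusion criterion 2, and show it in Table 2 if it is made at screening.
- Check Figures 1 to 3 against the revised order.

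The cost is wording and a changed order of steps, with no new procedures or randomised patients. A few T0 batteries will be spent on people who are then not randomised. The change protects the baseline only. Knowledge of the arm at T1 to T3 remains a consequence of having no sham, a limitation the article already acknowledges.
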